### Treatment protocol

PCT is a manualized, individual cognitive behavioral treatment for adults with PD (with or without agoraphobia) [64]. Patients are helped to become panic-free by learning to anticipate and respond to situations that trigger their panic attacks and to manage the physical symptoms of panic using techniques such as controlled breathing. PCT ordinarily consists of 12 weekly therapy sessions. In the current trial, PCT involves 12 to 14 sessions completed within 10 to 16 weeks; week 1 includes 2 sessions and subsequent weeks 1 session each. Between 2 and 5 sessions will include therapist-assisted exposure. Each session is 60 minutes in duration, extended to 90 to 120 minutes for those including therapist-assisted exposure. Total treatment duration will be 780 to 1,140 minutes.

Session 1 of PCT involves psycho-education about the nature of PD and agoraphobia. In Session 2 the patient learns the importance of (and how to) recording their daily levels of anxiety/panic so that they can monitor progress alongside their therapist. Sessions 3 to 12 involve cognitive restructuring of anxiety-related cognitions and structured, therapist-guided exposure to situational/somatic cues that may be associated with panic attacks and agoraphobic avoidance. A single session teaches clients how to slow their breathing rate to counter the effects of hyperventilation.

PFPP is a manualized, individual psychodynamic treatment for adults with PD (with or without agoraphobia) [38]. Treatment is ordinarily 19 to 24 sessions in length with 2 sessions per week, 45 minutes each. PFPP delivered in the current trial comprises 19 to 24 sessions completed within 10 to 16 weeks; in principle 2 sessions per week, 45 minutes each. Total treatment duration will be 855 to 1,080 minutes.

PFPP proceeds in three phases. In Phase I the therapist works to identify the specific content and meanings of the panic episodes and to help the patient examine the stressors and feelings surrounding the onset and persistence of panic. Specific vulnerabilities to the development of panic from the patient’s past are explored (for example, representations of parents, traumatic experiences, difficulty expressing and managing angry feelings). The patient is aided in bringing forth fantasies and feelings that may have been unconscious or difficult to tolerate, such as vengeful wishes or abandonment fears, and to identify intra-psychic conflicts surrounding anger, separation, and sexuality. The goal of this phase is reduction in panic symptoms.

Phase II seeks to address the dynamics that maintain vulnerability to panic and the persistence of panic symptoms (for example, difficulties with anger recognition and management, separation, and fears of loss or abandonment). These dynamics are addressed through discussion of the patient’s feelings/fantasies about past/present relationships and in the transference relationship with the therapist. Improved understanding of these conflicts helps to prevent the development of a vicious cycle of PD recurrence.

In Phase III the therapist and patient work with the patient’s conflicts with anger and separation as they emerge in the context of termination. Increased assertiveness and the capacity to communicate about conflicts in relationships should improve quality of life and reduces panic vulnerability. Thus the patient is helped to experience and articulate their feelings about loss and anger directly with the therapist to facilitate better management of these feelings and the capacity to avert the development of more severe panic states.

### Treatment integrity

Treatment integrity refers to the degree to which an intervention is delivered as intended. Therapists in the trial provide only one form of treatment during the study and the vast majority will provide only CBT or only PDT as part of their usual practice. Treatment integrity encompasses three aspects: a) therapist treatment adherence (the degree to which the therapist utilizes prescribed procedures and avoids proscribed procedures); b) therapist competence (the level of the therapist’s skill and judgment); and c) treatment differentiation (whether competing treatments differ from each other along critical dimensions).

All three aspects of treatment integrity are addressed throughout the trial in keeping with the standards for the field proposed by Perepletchikova *et al*. [65]. The first two aspects are addressed firstly through training and supervision of trial therapists in PCT and PFPP prior to their participation in the study. Prior to commencement of patient recruitment therapists and supervisors receive workshops in PCT and PFPP and additional workshops are arranged each year of the trial. Therapists must also treat as per-protocol (videotaping sessions) a ‘training’ case under supervision from a trial-trained supervisor. Videotapes from this therapy are evaluated by another experienced supervisor of PCT or PFPP for treatment adherence. During the trial therapists continue to videotape treatment sessions and to receive supervisions from a trial-trained supervisor. The supervisor rates therapist adherence during supervision and provides feedback to the therapist about the same. Adherence is also controlled for each patient therapy by three ratings (beginning, middle and end of therapy) made by independent raters with feedback from these ratings given to trial supervisors to use with therapists. A minimum of three site visits per annum from the research team are scheduled to ensure (improve) site protocol adherence.

### Project implementation plan

Point prevalence of PD in the Swedish general population is 2 to 3% [5], which means that over 40,000 individuals currently have PD in the regions of Halland, Skåne and Dalecarlia. Given an inclusion period of 6 years (2011 to 2016) about 40 patients have to be recruited each year. Trial therapists are expected to treat about three patients each per year. The study is carried out at 10 sites in the counties of Skåne (Lund, Malmö, Eslöv, Arlöv and Trelleborg), Halland (Halmstad, Falkenberg and Varberg), Jönköping (Värnamo) and Dalecarlia. All participating therapists work in primary healthcare centers or psychiatric outpatient clinics. Currently, 35 therapists are active in the project. All clinics have signed written agreements to supply the project with patients during the inclusion phase. Intake and treatment of patients began in 2011. This phase is scheduled to last 5 years until 2016. Follow-up studies will be completed in 2018.

### Power/sample size calculations

For the planned and relatively straightforward comparisons between the 2 active treatments (PCT and PFPP) and wait-list, 25 patients per group would be needed in order to ensure an effect size (Cohen’s *d*) of 0.8 at alpha = 0.05 and power = 0.80. Our assumption of an effect size difference versus wait-list of *d* = 0.8 is conservative relative to the average controlled effect size (*d* = 1.02, 95% CI = 0.86 to 1.18) reported in a recent meta-analysis of 61 RCTs comparing psychological treatments for PD to no treatment or psychological/drug placebo [17]. For the planned and straightforward comparison between the randomized and self-selection conditions, we have assumed that the difference between the two conditions will be in the order of *d* = 0.4. Again our assumption is conservative relative to the average effect size obtained for self-selection versus randomization in preference trials involving treatments for anxiety (*d* = 0.49, 95% CI = 0.19 to 0.79), albeit based on a much smaller number of RCTs [66]. For the more complex comparisons involving the hypothesized interaction between assignment type (randomization or self-selection) and treatment type (PCT or PFPP), power calculations have been performed based on the PINT (Power IN Two-level designs, v. 2.12, September 2007) [67,68]. In the absence of *a priori* information about the size of the interaction effect between assignment and these 2 specific treatments, we assume the interaction effect size will be comparable in size to the main effect size for assignment (that is *d* = 0.40). At alpha = 0.05, power = 0.80 and *d* = 0.4, a total of 200 patients is required. Assuming a 15% drop-out rate, a total of 212 patients is required.

After consideration of issues pertaining to practicality of randomization, the target recruitment is N = 216. This was based on the following tentative assumptions, among others: Assignment (randomized versus self-selected) is a fixed effect on Level 1 with M = 0 and SD = 1; the Pre-treatment measure is a random and fixed effect on Level 1; Treatment (PCT versus PFPP) is a Level 2 predictor with M = 0.0625 (given a 55:45 distribution in the self-selection group) and SD = 1; residual variance in post-treatment = 0.70; and explained variance on outcome across therapists = 0.05.

The 216 patients will be randomly allocated to the randomized condition, the self-selection condition or to the waiting-list in the following shares: 108: 108: 26 (see Figure 1 for Consolidated Standards of Reporting Trials (CONSORT) flow chart). After 3 months patients on the waiting-list will be re-randomized to randomization or to self-selection. The self-selection condition allows the patient to choose either PFPP or PCT. The actual choice is made after reading a detailed and well-balanced presentation of the two alternative therapies. These presentations have been developed and tested in an unpublished study by [name].

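### The scale of the interaction effect (d = 0.40) is not defined; 200 patients give 80% power only for a difference of differences of about 0.7 to 0.8 SD

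*Protocol article*

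**What the plan says.** The section on power and sample size in the protocol article covers three comparisons. For self-selection against random assignment it states: "we have assumed that the difference between the two conditions will be in the order of *d* = 0.4". Here d is plainly a difference between two group means in SD units.

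For the interaction between assignment type and treatment type, the calculation was done in the two-level program PINT. There was no prior information on the size of this effect, so the authors write "we assume the interaction effect size will be comparable in size to the main effect size for assignment" and give the value 0.40. The result is: "At alpha = 0.05, power = 0.80 and *d* = 0.4, a total of 200 patients is required". The later totals of 212 and 216 build on this figure.

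The listed inputs give both predictors an SD of 1, with mean 0 for assignment and 0.0625 for treatment, and add "residual variance in post-treatment = 0.70; and explained variance on outcome across therapists = 0.05". The text calls these assumptions tentative and presents them as a partial list. It does not say whether the interaction d is the full difference between the two assignment effects or a coded contrast.

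**The concern.** An interaction is a difference between two differences, each estimated in half the sample. On the raw SD scale its standard error is twice that of the main effect, so an interaction of the same raw size needs about four times as many patients. Yet 200 is also the total for a plain two-group comparison at d = 0.40. A reader who takes the sentence at face value will believe the trial has 80% power to detect that choice is worth 0.40 SD more in one therapy than in the other.

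What is at stake is how a null interaction can be used. The article describes the interaction as hypothesized, and interactions of preference with other moderators are among its aims. If the test is believed to have 80% power at 0.40 SD, a non-significant result could be taken as evidence that choice helps equally under PCT and PFPP.

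**Working it through.** **Inputs.** From the section on power and sample size: alpha 0.05, power 0.80, d = 0.40, N = 200, predictor SD = 1, residual variance 0.70, therapist variance 0.05, a 55:45 split among those who choose, drop-out 15%, target 216. From the project implementation plan: 35 therapists. Assumption: two-sided test, since the sidedness is not stated.

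**1. The plan's figure.** A two-group t-test at d = 0.40 needs 99.08 per group, so 100 per group and 200 in total (the normal approximation gives 198). The number 200 is therefore reproduced as a main-effect sample size.

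**2. Standard errors with four equal cells, outcome variance v.**
- Main effect: sqrt(4v/N). At v = 1, N = 200 this is 0.141. Power at 0.40 is Φ(0.40/0.141 − 1.96) = 81%.
- Difference of differences: sqrt(16v/N). At N = 200 this is 0.283 for v = 1 and 0.237 for v = 0.70.

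**3. Reading A: 0.40 is the full difference of differences.**
- N = 200, v = 1: Φ(0.40/0.283 − 1.96) = 29%.
- N = 200, v = 0.70: Φ(0.40/0.237 − 1.96) = 39%.
- At 216 × 0.85 ≈ 184 completers: 27% and 37%.
- N for 80% power: 16v(2.80/0.40)², about 785 for v = 1 and about 550 for v = 0.70.

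**4. Reading B: 0.40 is the contrast on -1/+1 coded predictors.** A balanced 0/1 factor has SD 0.5; an SD of 1 corresponds to -1/+1 coding. All coefficients then have standard error sqrt(v/N). A main effect of d = 0.40 is a coefficient of 0.2. An interaction coefficient of 0.2 corresponds to a difference of differences of 4 × 0.2 = 0.80 SD.
- N = 200, v = 1: Φ(0.80/0.283 − 1.96) = 81%.
- N = 200, v = 0.70: 92%.
- N for 80% power at v = 1: 16(2.80/0.80)², about 197.

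**5. Size detectable with 80% power,** 2.80 × sqrt(16v/N):

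| N | v = 1 | v = 0.70 |
|---|---|---|
| 200 | 0.79 SD | 0.66 SD |
| 184 | 0.83 SD | 0.69 SD |

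**6. Sensitivity.** The 55:45 split changes power by less than 0.3 percentage points. A two-level calculation with 35 therapists, treatment at therapist level, therapist variance 0.05 and residual variance 0.70 gives the same standard error, 0.059, for the assignment and interaction coefficients. Power is 39% under reading A and 92% under reading B. Adding a therapist variance of 0.05 in the assignment effect (an assumption; the article does not state one) gives 30% and 81%.

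**The case against.** The strongest defence is the coding. Predictors with SD 1 point to -1/+1 coding, under which main effect and interaction have equal standard errors, so an interaction equal in coded size to the main effect has the same power. On that reading the stated 80% is met or exceeded at 200 patients. This stands, and it means no sum in the section is shown to be wrong.

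A reader might go further and infer that 200 is really a main-effect number carried over to the interaction, so that true power is 29% to 39% without qualification. The documents do not support that. The article says the calculation was run in PINT. With equal coded effects and variance 1, the interaction calculation also returns about 200, so the match with a t-test does not show where the figure came from. Nor does the failure of a simple calculation with residual variance 0.70 to return exactly 80% prove an error. The input list is openly partial, cluster size and any random-slope variance are not given, and one plausible slope variance brings reading B back to 81%. A condensed article may leave those inputs to the full protocol.

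It is also fair to say that the primary aim concerns the influence of preference, for which 200 analysed patients are adequate at d = 0.40, and that the article nowhere says a null interaction will be read as no interaction.

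The defence does not remove the ambiguity. Reading B saves the 80% by making the target effect 0.80 SD. That equals the effect the same section assumes for active therapy against wait-list, and is twice the assumed average effect of choice. The sentence does not convey this.

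**Conclusion.** The point holds as a defect of definition with a material numerical consequence. The article does not state the scale of the interaction d. On the scale it uses for the main effect, power for an interaction of 0.40 SD is about 29% to 39% at 200 patients and 27% to 37% at 184. On the coded scale, the 80% is right but refers to a difference of differences of 0.80 SD. Under either reading, 200 patients give 80% power only for a difference of differences of about 0.66 to 0.79 SD, not 0.40.

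These figures assume a two-sided test, near-equal cells and variance between 0.70 and 1. Which reading the authors intended cannot be determined, because the PINT run cannot be rebuilt from the inputs given.

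**What to change.** In the section on power and sample size:
- Define the interaction effect as a difference of differences in SD units, and say which value the PINT calculation used.
- State that about 200 analysed patients give 80% power for self-selection against random assignment at d = 0.40, and for the interaction only at about 0.7 to 0.8 SD.
- Give the power for a 0.40 SD difference of differences: about 30% to 40% at 200 patients, slightly less at 184.
- Commit to reporting the interaction with a confidence interval and not to interpreting non-significance as absence of an interaction.

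Labelling the interaction as exploratory is optional; the finding does not require it. The cost is wording only. No extra patients are needed, but the stated sensitivity of the interaction test becomes less favourable.

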What about attrition in CBT and pharmacotherapy? PD patients fear somatic symptoms and often the medical side effects that can accompany pharmacotherapy, and these fears may represent a major reason why PD patients often refuse medication when first offered (pre-treatment attrition) or why as many as one third prematurely discontinue pharmacotherapy once begun [28,29]. Limited data is available about pre-treatment attrition in relation to CBT. In a study of 731 patients (22% with PD) presenting to a specialist anxiety service, all of whom were offered CBT outside of a clinical trial, the authors found that 30% dropped out before commencing CBT with 12.6% actively refusing CBT [30]. Although drop-out from CBT once begun was relatively low in the previous study (10.7%), a meta-analysis of RCTs by Haby *et al*. involving patients with either primary PD, Generalized Anxiety Disorder, or depression reported an average drop-out rate of 17% for PD patients treated with CBT (range = 0 to 54%) [18].

The dominance of CBT in the treatment of anxiety over the past two decades has meant that relatively few RCTs have been carried out comparing this approach to another active psychological treatment [31,32]. The majority of comparative psychotherapy trials for patients with PD have involved two forms of CBT (for example, cognitive versus behavioral, with/without therapist-guided exposure, self-help, Internet-based, and so on). Psychodynamic therapy (PDT) is an evidence-based treatment for a range of conditions involving a significant anxiety component [32,33]. While much fewer RCTs of PDT exist than for CBT, meta-analytic reviews have been carried out to estimate the effectiveness of PDT for a range of problems including anxiety [34-38]. In the 2 most recent [35,36], PDT was observed to be no less effective for anxiety than other active treatments in the short or long term, had similar drop-out rates (17%) as reported for CBT, and yielded controlled effect sizes relative to no/minimal treatment or treatment as usual in the medium range (*g* = 0.63). These effects were persistent at follow-ups of 6 to 12 months; however, the limited number of trials (focused primarily on social anxiety) and the significant heterogeneity between trials limits the conclusions that can be drawn [36]. Further comparative trials involving PDT and CBT are needed [13].

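### The sample-size figures of 200 required, 15% drop-out and 212 to recruit cannot all be right, and neither 212 nor the 216 target leaves 200 patients after 15% drop-out

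*Protocol article*

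**What the plan says.** All the figures stand in the protocol article under Power/sample size calculations. After describing a two-level power calculation (PINT) for the interaction between assignment type and treatment type, the authors write that "we assume the interaction effect size will be comparable in size to the main effect size for assignment", that is d = 0.40. They conclude: "At alpha = 0.05, power = 0.80 and *d* = 0.4, a total of 200 patients is required". The next sentence reads: "Assuming a 15% drop-out rate, a total of 212 patients is required". The following paragraph adds: "After consideration of issues pertaining to practicality of randomization, the target recruitment is N = 216". Among the assumptions listed for this target are "residual variance in post-treatment = 0.70; and explained variance on outcome across therapists = 0.05".

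The same section then splits the 216 patients as 108 to random assignment, 108 to self-selection and 26 to the wait-list, and says that wait-list patients are re-randomised after three months. The Abstract also gives 216 as the trial size.

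**The concern.** The step from 200 to 212 is presented as an allowance for 15% drop-out, but an increase of 12 on 200 is only 6%. If 200 evaluable patients are what 80% power requires, and 15% are lost, then neither 212 nor 216 leaves enough. A reader of the published justification would believe that the trial keeps 80% power after the assumed drop-out. On the document's own figures it does not. The rounding up to 216 does not repair this: it is attributed to the practicality of randomisation, not to attrition, and it is still too small.

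**Working it through.** **Inputs**, all from Power/sample size calculations: alpha 0.05 (sidedness not stated, so two-sided is assumed here), power 0.80, d = 0.4, 200 required, 15% drop-out, 212 after inflation, target 216.

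**Step 1: the base figure.** For a two-group comparison, the normal formula n per group = 2(1.960 + 0.842)² / 0.4² gives 98.1, so 99 per group and 198 in total. The t-test version gives 99.08, so 100 per group and 200 in total. The stated 200 is therefore reproduced by a simple two-group calculation. The PINT run itself cannot be repeated from the published inputs.

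**Step 2: the inflation.**
- N/(1 − 0.15) = 200/0.85 = 235.3, so 236. Check: 236 × 0.85 = 200.6.
- The cruder rule N × 1.15 = 230.
- Starting from 198 instead gives 233 or 228.

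None of these is 212 or 216. The shortfall against 236 is 24 patients for 212 and 20 for 216.

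**Step 3: what the stated totals do allow for.**
- 1 − 200/212 = 5.7% drop-out.
- 1 − 200/216 = 7.4% drop-out.

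**Step 4: what is left at 15% drop-out.**
- 212 × 0.85 = 180.2.
- 216 × 0.85 = 183.6.

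**Step 5: power at those sizes.** Two-sided two-group t-test at d = 0.40, equal groups:

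| Evaluable | Power | d detectable with 80% power |
|---|---|---|
| 200 | 80.4% | 0.398 |
| 183.6 (from 216) | 76.9% | 0.416 |
| 180.2 (from 212) | 76.1% | 0.420 |

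The normal approximation gives 80.7%, 77.3% and 76.6%. This is a proxy: it ignores therapist clustering and treats the interaction contrast as being as precise as the main effect of assignment, as the plan's 200 appears to do.

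**Step 6: which figure could be the slip.** 180/0.85 = 211.8, which rounds up to 212. So 212 would be right for a base of 180 at 15%, or for a base of 200 at about 5.7%. The text states 200 and 15%, and offers nothing to decide between these explanations.

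**Step 7: the allocation shares.** 108 + 108 + 26 = 242, while 108 + 108 = 216.

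**The case against.** **The total may really be 242.** The shares sum to 242, and 242 × 0.85 = 205.7 would cover 200. Two other statements lean that way: about 40 patients a year over six years is about 240 (Project implementation plan), and 138 recruited is called a little over half of the target (Trial status), which is 57% of 242 but 64% of 216. Against this, the Abstract and two places in the power section give 216. Because wait-list patients are re-randomised into the two conditions, the 26 may already be counted in the two groups of 108. What stands is that the total needs clarifying. It does not make 212 follow from 200 and 15%.

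**The effect is small.** This stands. The proxy loss is about 3 to 4 percentage points, and a mixed model that uses partial data from patients who drop out could reduce it further.

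**Baseline adjustment might restore the power.** A reader could put the listed residual variance of 0.70 into the simple formula and find ample power at 184. The documents do not support that. The residual variance and the pre-treatment measure are already among the assumptions listed for the target, so they cannot be credited a second time. Under that formula 80% power would need only about 138 patients, which cannot sit beside a requirement of 200. It also describes the simple contrast of self-selection with random assignment, without therapist clustering, whereas the 200 follows the interaction calculation.

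**The 15% might itself look too low.** The Background "reported an average drop-out rate of 17% for PD patients treated with CBT", and a reader might infer that 15% should be raised. But that source has a range of 0 to 54%, and the Background also cites 10.7% for CBT once begun and 7% for PFPP. The assumed 15% lies within what the document cites, so this is not part of the point.

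**Conclusion.** Wrong as written. The figures 200, 15% and 212 are mutually inconsistent, and no standard inflation rule turns 200 into 212 or 216. Taking 200 and 15% as stated, the requirement is 236. The 216 target leaves about 184 evaluable patients and 212 about 180. The claimed 80% power at d = 0.40 is then about 77% or 76% in the two-group proxy, with a detectable d of about 0.42. This rests on a two-sided alpha and on treating drop-outs as contributing no data. The loss under the two-level model is unknown.

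Two stronger readings should be resisted. The first is that 236 is certainly the correct number: the slip could equally lie in the base figure or in the drop-out rate. The second is that the trial is seriously underpowered: the proxy loss is modest. The error lies in a stated justification that the trial relies on, and it can be corrected.

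**What to change.** 1. Check 200, 15% and 212 against the original PINT run and correct whichever is wrong.
2. If 200 and 15% both stand, state the inflated requirement as 236 and delete the statement that 212 suffices.
3. If recruitment stays at 216, state that about 184 patients are expected to be evaluable after 15% drop-out. Report the power from the same two-level model re-run at that size for the assignment-by-treatment interaction. The simple proxy suggests roughly 77%, but the re-run figure is the one to print.
4. In the same revision, reconcile the 108:108:26 shares with the 216 total, saying whether the 26 wait-list patients are counted again in the two groups of 108.

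The cost is one re-run of an existing calculation and a few sentences, with a slightly less favourable power figure if 216 is kept. Raising the target to 236 would mean 20 more patients. That was still possible when the article was written, since recruitment was ongoing at 138.
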